# 2.0 PROTOCOL SUMMARY

Title: Post-acute Structured Exercise Following Sport Concussion: a Randomized Controlled Study

Overview: This study will investigate the effect of structured, structured aerobic exercise protocol (SAEP) compared to usual care on clinical recovery from sport-related concussion (SRC) within the post-acute phase of injury. Participants will be randomized into one of two groups: (1) Supervised Exercise Group: participants will complete a total of eight exercise sessions over the course of 11 days, starting at Day 3 post-injury (two sessions (first and mid-point) will be done in the lab, and the remained will be home-based sessions); (2) Usual Care Group: individuals will undergo a period of physical rest and standard care. For the purposes of this study, "rest" will be defined as the avoidance of any activities beyond those of daily living, including participation in sport and physical activity.

Objectives: *Primary:* To investigate the utility of an SAEP initiated in the sub-acute phase after SRC in reducing post-concussion symptoms and the time to medical clearance, compared to usual care. *Secondary:* To determine the effect of an SAEP in concussed subjects on ANS function, blood biomarkers, and cognition

Outcome Measures: *Primary*: post-concussion symptom scores and days to medical clearance; *Secondary:* a) cardiovascular responses [heart rate variability (HRV) and blood pressure variability (BPV)], b) cognitive performance, and c) neuroinjury/neuroreparative blood biomarkers (BDNF, glial fibrillary acidic protein [GFAP], peroxiredoxin [PRDX]-6, monocyte chemoattractant protein [MCP]-1), and catecholamines (norepinephrine [NE] and epinephrine [Epi]).

Endpoints: *Primary:* Days to asymptomatic status and days to medical clearance *Secondary:* Cardiovascular, cognitive, and neuroinjury markers at Day 90 post-injury.

Population:

Age: 13-25 years, Sex: All

Inclusion Criteria:

Diagnosed with SRC by a physician at the David L. MacIntosh Sport Medicine Clinic

Able to speak and understand English

Exclusion Criteria:

Have had a previous concussion within two weeks of the presenting SRC

Have any co-morbid injuries (i.e. musculoskeletal/soft-tissue injuries, vestibular disorders)

Have a pre-existing heart condition

Have any uncontrolled seizure disorders or a history of medical or neurological conditions that affects cognitive functioning

Number of Sites: 1

Study Duration: 36 months

Participant Duration: 90 days

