## 9.1 Participants

Participants will be recruited from the David L. Macintosh Sport Medicine Clinic (University of Toronto). The Macintosh Clinic is an interdisciplinary sport medicine clinic with a Concussion Program. The clinic is known for their acute management of concussions and is the primary clinical site for University of Toronto students who sustain physical activity related injuries. The clinic also has a number of existing relationships with local district schoolboards and sports organizations. These organizations are not founded on research participation, and do not require physician referral for concussion. The most recent estimate of new concussion cases in the clinic per year is approximately 300-350. Based on our previous research conducted at the MacIntosh Clinic^1,2^, as well as recent Canadian emergency department statistics^14^, we expect female participants to account for 40% of our study sample. Potential study participants will be examined and diagnosed with SRC within 72 hours of injury by one of the 3 physicians working at the clinic who specialize in concussion management. If the patient is diagnosed with a concussion, informed consent and study enrolment will occur after the first office visit. At Day 3 post-concussion, study eligibility will be confirmed by a Post-Concussion Symptom Scale (PCSS) evaluation used to determine their symptom status. The decision to wait three days post-injury to randomize participants and initiate the intervention is aligned with an approach based on the suggestion that rest beyond three days following mTBI is provides no further benefit to recovery^16^. At that time, symptomatic patients (defined as having a PCSS score equal to or greater than five on the SCAT5) will be randomly divided into one of two groups by a computer generator; this task will be overseen by a member of the research team not involved in the consent process. Our operational definition of “symptomatic” status (PCSS score 5 or greater) is based on prior literature, including a systematic review by Alla and colleagues, which suggests low PCSS scores are representative of the general population’s symptom presentation in a non-concussed state^77^**.**

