## 9.2 Intervention

**(1) Usual care (UCEP) group:** Participants allocated to the UCEP group were advised to follow the instructions, prescriptions, and recommendations given to them by the sport medicine physician. Aligned with consensus guidelines of a brief period of physical and cognitive rest, the physician advised participants to increase their activity levels gradually with minimal head movement (predominantly involving a stationary bike) and progressively increase levels of exertion while remaining under the threshold of symptom exacerbation.^78^ Subsequently, exercise included a progression of head movements, visual and cognitive burdens, sport-specific activities, and heavy resistance, in that order, all below the symptom exacerbation threshold. For more details on the UCEP, please see the **Appendix**. Any diagnosed concomitant neck injuries underwent concurrent rehabilitation. Completion of asymptomatic low-risk simulations of target activities was required prior to medical clearance to return to those activities.

**(2) Structured Aerobic Exercise Protocol (SAEP) group:** These individuals will begin to exercise at Day 3 post-injury. Participants will be asked to complete a total of eight exercise sessions over the course of 11 days, with one day of rest after two consecutive sessions. The participants will have their symptoms recorded before and after exercise, and monitored throughout each session. Symptoms will only be recorded during exercise if exacerbated, in which case the session will be terminated. If this occurs, patient will resume the same stage in the protocol at the subsequent session. If the patient’s symptoms become exacerbated for two consecutive sessions, they will be removed from the study and continue with clinic for patient follow-up. Should the participant achieve asymptomatic status at any point, they will continue with the exercise protocol until completion, while simultaneously being guided through the RTP guidelines.

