## 9.5 Structured Aerobic Exercise Protocol (SAEP)

The proposed exercise protocol will consist of 8 sessions, proceeding in a stepwise fashion with respect to duration and intensity over the course of 11 days, with two consecutive sessions proceeded by one day of rest. A fixed wattage stationary bike (Velotron Dyndafit Pro, manufactured by Racermate Inc., Seattle, WA, USA) will be used for all exercise sessions. The use of a stationary bike will ensure head and neck stability, avoiding any unwanted accelerations of the head (cf. treadmill). Finally, the bike will be connected to an interactive heart rate monitor (Polar®, Kempele, Finland), allowing the research team to control the wattage of the bike for each individual subject.

The first session of the AE protocol will take place on the Day 3 post-injury, and will comprise 15 minutes of steady-state exercise at 60% of the participant’s age-predicted maximal HR (apHR), plus a warm-up and cool-down period (25 minutes total). The participant’s symptoms will be monitored before, during, and after exercise. If the participant’s symptoms are not exacerbated, they will proceed to the next exercise level, consisting of 20 minutes of steady-state exercise, at 60% of apHR, plus warm-up and cool-down (30 minutes total). Please see **Table 1.** below for a detailed summary of the exercise protocol. Participants’ HR and BP will be recorded before and after each exercise session. Symptoms will also be recorded before and after each exercise session using the PCSS, and a trained kinesiologist will monitor symptoms throughout the exercise session. A prepared script to monitor symptoms has been developed to ensure standardization. If participants in the exercise group achieve asymptomatic status at the two weeks post-injury, they will continue to progress through the AE intervention until they complete all eight sessions, and will also begin progressing through the existing clinical RTP guidelines.

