In an effort to improve our ability to evaluate the efficacy of the intervention, all participants will be given an activity tracker. The benefit of providing an activity tracker is the ability to monitor and quantify activities with daily living (ADL) beyond the study protocol (Supervised Exercise Group or Usual Care Group). Participants will be provided activity tracker (Fitbit Alta HR) at the time of consent to participate in the study and returned to the researcher at Day 28 assessment. Data to be collected by Fitbit Alta HR include steps (daily) and heart rate (daily per beats per min); this data will be used as potential co-variates when evaluating the efficacy of the intervention.

**Table 1.** AE exercise protocol

|  |  |  | **AE Protocol** | | | | | | | | |
| --- | --- | --- | --- | --- | --- | --- | --- | --- | --- | --- | --- |
| Day | 3 | 4 | 5 | 6 | 7 | 8 | 9 | 10 | 11 | 12 | 13 |
| Session | 1 | 2 | Rest | 3 | 4 | Rest | 5 | 6 | Rest | 7 | 8 |
| Duration (min) | 15 | 20 |  | 20 | 20 |  | 20 | 20 |  | 20 | 20 |
| Intensity (% apHR) | 60 | 60 |  | 65 | 65 |  | 70 | 70 |  | 75 | 75 |

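### Section 9.5 lets post-randomisation tracker data enter the efficacy evaluation as covariates, which can bias the treatment effect and does not match the covariate list in 14.1

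*Protocol*

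**What the plan says.** Section 9.5 of the protocol provides all participants, in both arms, with a tracker "at the time of consent to participate in the study and returned to the researcher at Day 28 assessment". It records daily steps and daily heart rate. The stated purpose is to "monitor and quantify activities with daily living (ADL) beyond the study protocol". The section then commits to a use: "this data will be used as potential co-variates when evaluating the efficacy of the intervention". That sentence is not limited to days before randomisation, and it is not labelled exploratory or mediation.

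Section 9.1 puts randomisation and the start of treatment at the same point, referring to "The decision to wait three days post-injury to randomize participants and initiate the intervention". Under section 9.2 the SAEP group is to "complete a total of eight exercise sessions over the course of 11 days, with one day of rest after two consecutive sessions". Table 1 places those sessions on Days 3 to 13, with intensity set by heart rate and rising from 60% to 75% of the age-predicted maximum.

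Section 14.1 describes a Cox model for time to medical clearance and names sex/gender, age and initial PCSS as the variables to control for. Neither 14.1 nor 14.2 mentions tracker data.

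**The concern.** A covariate in a randomised comparison should not be something that treatment can change. Tracker data fail that test in three ways.

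- **On the pathway.** The intervention is exercise dosed by heart rate. If part of its benefit comes through greater activity or altered heart rate, holding those fixed removes that part from the estimate.
- **Shared causes.** Participants with milder injury probably move more and also clear sooner. Once activity differs between arms, comparing people at equal activity means comparing people of unequal severity, and randomisation no longer protects the contrast.
- **Consequence of the outcome.** Participants who recover before Day 28 become active because they have recovered. A summary up to Day 28 then carries information from after the event it is meant to help explain.

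An adjusted hazard ratio of this kind would not estimate the effect of being allocated to SAEP, and an effective programme could look weak. Because the two sections give different covariate sets, the choice between them could also be made after results are seen.

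**Working it through.** **1. Timing.** The tracker is issued at consent, which follows a first visit within 72 hours of injury (9.1). Randomisation is on Day 3 and the tracker is returned at Day 28 (9.5). Days after randomisation: 28 - 3 = 25. Days before it: at most 3. The post-randomisation share is therefore at least 25/28 = 89%, and close to 100% for someone who consents on Day 3.

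**2. How many could be cleared while still in the tracker window.** Section 13.0 gives a mean of 43 days (SD 20) for usual care and a target of 36 days. Assuming a normal distribution and the same SD in both arms:

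- Usual care: (28 - 43)/20 = -0.75, so about 23% are cleared before Day 28.
- SAEP: (28 - 36)/20 = -0.40, so about 34%.

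For these participants a Day 28 summary would include activity recorded after clearance.

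**3. Size, as an illustration only.** The protocol has no figure to reproduce here. A linear model on days to clearance stands in for the Cox model:

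- Activity (SD 1 within arm): A = d·T + r·U + noise
- Days: Y = 43 - 7(1 - m)·T + b·A + c·U + noise, with b = -7m/d

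T is allocation and U is underlying health. The total effect is -7 days (13.0). *Assumed, because the document does not give them:* d, the shift in activity caused by SAEP (0 to 1.0 SD); m, the share of benefit passing through measured activity (0 to 100%); r, the correlation of health with activity (0 or 0.4); and c, -8 days per SD of health when r is 0.4.

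The within-arm slope of Y on A is b + c·r, so for d > 0

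adjusted effect = -7 - (b + c·r)·d = -7(1 - m) - c·r·d.

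*No shared cause (r = 0):*

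| Share through activity | Formula, days | Simulated, days |
|---|---|---|
| 25% | -5.25 | -5.1 to -5.3 |
| 50% | -3.5 | -3.2 to -3.5 |
| 75% | -1.75 | -1.6 to -1.9 |
| 100% | 0 | about 0 |

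The simulation used 53 per arm, 1,000 runs per setting and shifts of 0.3, 0.5 and 1.0 SD. At d = 0.5 and m = 50%, power fell from about 42% to about 15% (two-sided 0.05).

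*Shared cause only (m = 0, r = 0.4, c = -8):* adjusted effect = -7 + 3.2d, which gives -6.0, -5.4 and -3.8 days at d = 0.3, 0.5 and 1.0. The simulation gave -6.0, -5.4 and -3.7.

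*The same, with initial PCSS in the model as 14.1 intends.* Assume that PCSS correlates 0.7 in size with U. Given PCSS, var(U) = 1 - 0.49 = 0.51, cov(A, Y) = -8 × 0.4 × 0.51 = -1.632, and var(A) = 1 - 0.16 × 0.49 = 0.9216. The slope is -1.632/0.9216 = -1.771, so the adjusted effect is -7 + 1.771d: -6.5, -6.1 and -5.2 days. The planned PCSS adjustment reduces this bias but does not remove it unless PCSS captures severity fully.

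*No shift (d = 0, so m = 0):* simulated -7.0 days with or without the covariate, so no harm.

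**4. Pre-randomisation covariates only.** The estimate stays at about -7 days in every setting.

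**The case against.** A reader might infer that the primary Cox model will contain tracker data and that its hazard ratio is therefore invalid. The protocol does not support that. Section 9.5 says only that the covariates are potential, and the section that defines the primary model names three baseline variables and no others. An analysis plan not shown here may settle the matter. This stands: the use is permitted, not fixed. It does not clear the sentence in 9.5, which states a use in the efficacy evaluation and sets no limit on timing or purpose.

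A reader might also infer that adjustment would cancel the very exercise under test. The tracker is meant for activity outside the protocol, and stationary-bike bouts of 15 to 20 minutes may add few steps (an assumption). This stands in part. But daily heart rate is not said to exclude the sessions, and activity outside them can also respond to allocation and to recovery.

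The activity contrast may be modest as well. The summary (2.0) defines rest for the usual care group as "the avoidance of any activities beyond those of daily living, including participation in sport and physical activity", whereas 9.2 has that group increasing activity gradually, largely on a stationary bike. Those two descriptions must be reconciled. Until they are, the larger assumed shifts are uncertain.

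Finally, every magnitude above depends on assumed inputs, and the shared-cause figures are smaller once initial PCSS is in the model. That is correct, and it is why the figures are ranges.

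**Conclusion.** The point holds in limited form. Section 9.5 allows variables measured almost entirely after randomisation to be used as covariates for efficacy, and this does not agree with 14.1. Following 9.5 can remove part or all of the treatment effect, or otherwise bias it. The document does not show that the primary analysis will do so.

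The size cannot be derived from the protocol. Under the stated assumptions a true -7 days becomes about -3.5 if half the effect runs through measured activity and about 0 if all of it does. With no such pathway it becomes -6.5 to -5.2 under the assumed shared cause with PCSS adjusted. It stays at -7 if allocation leaves the tracker measures unchanged. These illustrations move toward zero because they assume SAEP raises activity. If SAEP participants moved less outside the sessions, the shared-cause bias would reverse sign.

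**What to change.** Replace the covariate sentence in 9.5, and add the same rule to 14.1, along these lines:

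> Efficacy comparisons will adjust only for variables measured before randomisation (sex, age, initial PCSS). Tracker data recorded after randomisation will not be covariates in these comparisons. They will be used to describe adherence and the difference in activity between arms, and may be used in a separately labelled exploratory analysis, for example of mediation.

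A tracker covariate built from the days before randomisation is not a useful substitute. That window is at most about three days and may be close to nil for participants who present late.

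The cost is a short statement in each of the two sections. Data collection, sample size and the baseline covariates already named in 14.1 do not change.

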## Measures

9.6.1 Clinical Assessment: At the first medical visit post-injury, participants will be evaluated by one of three treating physicians at the MacIntosh Clinic. The clinical assessment includes Sport Concussion Assessment Tool-5 (SCAT5), which includes information about the mechanism of injury, medical history, symptoms (PCSS), cognitive abilities, physical examination, and additional injuries/co-morbidities. Clinical management and corresponding follow-up evaluations will be at the discretion of the caring physician. Date of medical clearance will be obtained from medical records.

9.6.2 Physician and Research Assistant Blinding: To minimize bias, physicians will be blinded to the randomization of participants to either SAEP or usual care groups. Furthermore, all participants will be specifically instructed not to inform their treating physician of their group assignment at any point throughout the duration of the study. In addition, the randomization procedure will be overseen by a member of the research team who is not involved with the consent process.

### 9.6.3 Assessments at Day 7, 14, 21, 28, and 90:

***HRV Assessment:*** Resting HRV will be based on variability in participants’ R-R intervals using the Polar heart rate V800 sports watch and corresponding chest strap heart monitor (Polar ®, QC, Canada). The research team will be able to extrapolate the ratio of low frequency (i.e. sympathetic activity) to high frequency (i.e. vagal activity) signals that appear on a beat-to-beat basis, per subject. Participants will be asked to lie down in the supine position to allow for set up and accommodation. HRV will be assessed for 5 minutes in the supine position, then, after a 1-minute accommodation period, a final 5 minute HRV assessment in the upright-seated position will be performed.

***BPV Assessment****:* BPV will be assessed non-invasively on a beat-to-beat basis using the Finapres NOVA figure cuff device (Finapres Medical Systems, Amsterdam, Netherlands) employing a similar protocol to the assessment of HRV; participants will undergo a 5 minutes accommodation period, at which point their BPV will be assessed for 5 minutes in the supine position. Following this, participants will be asked to assume an upright-seated position, followed by a one-minute accommodation period and an additional five-minute assessment period in the upright-seated posture. Time and frequency domain measures of BPV will be recorded and digitally uploaded for each posture (not including the accommodation periods), as well as throughout the transition from one posture to the next, in order to determine the balance of sympathetic versus parasympathetic influence on the ANS.

***Blood Samples:*** Peripheral blood samples (approximately 20 mL) will be drawn from participants by a trained phlebotomist. Blood will be drawn on days 7, 14, 21, 28, 90 and 180 days post-injury in both groups, but before the onset of exercise in the SAEP intervention group. Specimens will be immediately centrifuged to isolate the plasma/serum, and aliquots will be stored at -70^ο^C until subsequent analysis. High sensitivity multiplexed immunoassay will be employed to quantitate inflammatory cytokines and chemokines, and CNS-injury specific biomarkers. In addition, radioimmunoassay will be employed to evaluate numerous neuroendocrine hormones.

***Cognitive Function:*** Using an iPad-based assessment tool (C3 Logix, Cleveland, OH, USA), participants will complete a series of tests designed to measure reaction time, information processing speed, visual acuity, and postural stability. This will take approximately 10-15 minutes to complete. The C3 Logix iPad system consists of seven modules for evaluation and takes approximately 17 min to perform. Four of the modules are based on long-standing traditional tests that have been translated to electronic form (i.e., Simple and Choice Reaction Test, Trails Test A & B, and symbol digit modalities test). C3 Logix also includes the most recent version of the Standardized Assessment of Concussion, which has been developed and recommended by the Concussion in Sport Group, and disseminated after the 5th International Conference on Concussion in Sport^16^.

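### HRV, BPV, blood and C3 Logix are first measured on Day 7, after three exercise sessions, and the section 14.2 model names no baseline covariate although usable pre-treatment scores are collected

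*Protocol*

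**What the plan says.** - **Assessment schedule.** Section 9.6.3, headed "Assessments at Day 7, 14, 21, 28, and 90", covers HRV, BPV, blood and the C3 Logix cognitive battery. It lists no earlier assessment of any of them.
- **Start of treatment.** Section 9.2 says of the exercise arm: "These individuals will begin to exercise at Day 3 post-injury". In Table 1 of section 9.5 the session row begins "Session | 1 | 2 | Rest | 3 | 4", set against Days 3, 4, 5, 6 and 7.
- **Collected before treatment.** The SCAT5 is done at the first medical visit (section 9.6.1), "which includes information about the mechanism of injury, medical history, symptoms (PCSS), cognitive abilities". Section 9.1 adds a PCSS on Day 3, before randomisation.
- **Analysis.** Section 14.1 adjusts time to clearance for sex/gender, age and initial PCSS. Section 14.2 sets out a group-by-time mixed model ANOVA for symptoms, HRV, BPV, cognition and biomarkers, and names no covariate. It counts six time points but lists five: Days 7, 14, 21, 28 and 90.
- **Blood.** Section 9.6.3 states "Blood will be drawn on days 7, 14, 21, 28, 90 and 180 days post-injury in both groups", and continues "but before the onset of exercise in the SAEP intervention group".

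**The concern.** Day 7 is the first value of every 9.6.3 measure, and by then the exercise arm has been treated for four days. Two things follow. No pre-treatment value of the same measure is available to absorb between-person variation, which is likely to be wide in a sample aged 13 to 25 of both sexes. A chance difference between arms in starting HRV, BPV, biomarker level or C3 Logix performance also cannot be seen directly.

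A statistical analysis plan cannot recover a baseline that was never collected. It can use the pre-treatment scores that do exist, but section 14.2 as written does not call on them, while section 14.1 does so for the primary endpoint.

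**Working it through.** **1. Exercise before the first assessment (Table 1).** Sessions fall on Days 3, 4, 6, 7, 9, 10, 12 and 13. Three precede Day 7, and a fourth falls on Day 7 itself. Steady-state minutes before Day 7: 15 + 20 + 20 = 55, out of 15 + 7 × 20 = 155 planned. All eight sessions are complete by Day 14.

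**2. Pre-treatment information by outcome.**

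| Outcome in 14.2 | Pre-treatment value in the protocol | Kind |
| --- | --- | --- |
| Symptoms | Day 3 PCSS | same instrument |
| Cognition (C3 Logix) | first-visit SCAT5 cognitive score | proxy |
| HRV, BPV | none of their own | age, sex and initial PCSS only |
| Biomarkers | none of their own | age, sex and initial PCSS only |

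On cognition, the protocol says "C3 Logix also includes the most recent version of the Standardized Assessment of Concussion". That module is the nearest counterpart to the SCAT5 score. The reaction-time, processing-speed, visual and balance tests are further from it.

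**3. What a covariate is worth.** The protocol gives no figure on this point. I take its 53 per group (section 13.0) as given; whether that number follows from its inputs is a separate question. The correlation r between covariate and outcome is not in the document, so the values below are assumptions.

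Adjustment multiplies the outcome variance by 1 − r². With two-sided alpha 0.05 and 80% power,

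detectable difference (SD) = (1.960 + 0.842) × √(2/53 × (1 − r²)).

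Unadjusted: 2.802 × √(2/53) = 2.802 × 0.1943 = 0.544.

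| r | 1 − r² | Detectable difference, SD | Equivalent n per arm, 53/(1 − r²) | Power for an assumed 0.5 SD |
| --- | --- | --- | --- | --- |
| none | 1 | 0.544 | 53 | 73% |
| 0.3 | 0.91 | 0.519 | 58 | 77% |
| 0.5 | 0.75 | 0.471 | 71 | 84% |
| 0.7 | 0.51 | 0.389 | 104 | 95% |

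The r = 0.7 row is an upper illustration for a baseline on the same instrument. It should not be claimed for a proxy.

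Section 14.2 also plans separate analyses by sex. With 40% females, 0.40 × 53 ≈ 21 per arm if balanced. The detectable difference there is 0.865 SD unadjusted, 0.825 at r = 0.3 and 0.749 at r = 0.5.

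**4. Why Day 7 cannot stand in.** Suppose the true effect is 0.5 SD at Day 14 and 0.25 SD is already present at Day 7 (both assumed). With equal SDs, adjusting for Day 7 estimates 0.5 − r × 0.25, that is 0.425, 0.375 and 0.325 for r = 0.3, 0.5 and 0.7. Part of the treatment effect is adjusted away.

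**5. Time points and draws.** Section 14.2 counts six time points and lists five. Section 9.6.3 lists six draws, the sixth on Day 180. Day 180 lies outside the 90-day participant duration in section 2.0 and the follow-up visits in section 9.0. The phrase "but before the onset of exercise in the SAEP intervention group" can mean before that day's session. It cannot mean before the intervention starts, because the first draw is on Day 7. The sixth time point could therefore be Day 180 or the remnant of an intended baseline. The document does not settle which.

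**The case against.** **The comparisons remain valid.** Hypotheses 2a and 2c are group differences at Days 14, 21 and 28, and the secondary endpoints are at Day 90; none is defined as change from baseline. Randomisation keeps these contrasts unbiased. This stands, and it limits the point to precision and description. A reader might infer that a benefit established by Day 7 and then constant would be missed. It would give no group-by-time interaction, but it would appear in the between-group effect, which section 14.2 names.

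**Covariates are often left to the statistical analysis plan.** Section 14.2 does not exclude them, and a plan not shown may already include them. This also stands. The covariate part is an improvement available at no cost, not an omission that invalidates the analysis. The Day 7 start is different, because the protocol itself fixes it.

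**The gain is uncertain.** All correlations are assumed. Proxy covariates may reach no more than 0.3, where the detectable difference moves only from 0.54 to 0.52 SD. Biomarkers with too few quantifiable samples go to a chi-square test, where this calculation does not apply.

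**Imbalance is not invisible.** Balance on age, sex, PCSS and SCAT5 cognition can be examined. Only imbalance on the 9.6.3 measures themselves cannot.

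**Conclusion.** The point holds for the 9.6.3 instruments. HRV, BPV, blood and C3 Logix have no scheduled pre-treatment value, three sessions precede their first assessment, and section 14.2 does not use the pre-treatment scores the trial collects. The cost is modest: the detectable difference is 0.54 SD where 0.52 (r = 0.3) or 0.47 (r = 0.5) might be reached. Proxy covariates are likely to be at the low end; Day 3 PCSS in the symptom model may do better.

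Two stronger readings are not supported:

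- A reader might infer that no secondary outcome has any pre-treatment information. SCAT5 cognition is recorded before treatment, as is PCSS for the symptom model.
- A reader might infer that the Day 180 draw is unused and could be moved to Day 3 at no cost, with the other measures added then. Its use is unresolved, and moving it would give up the only sample after Day 90. It would also serve biomarkers alone. Day 3 HRV, BPV and C3 Logix would be new procedures for up to 2 × 53 = 106 people, and the protocol does not say that usual-care participants attend in person on Day 3.

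**What to change.** In section 14.2, or in the statistical analysis plan if it does not already say so:

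1. Adjust the symptom model for Day 3 PCSS.
2. Adjust the cognitive outcomes for the first-visit SCAT5 cognitive score, described as a proxy.
3. Carry age, sex and initial PCSS from section 14.1 into the other secondary models, dropping sex from the sex-specific ones. State whether initial PCSS means the first-visit or the Day 3 score, since both are collected.
4. State that Day 7 is an outcome and will not be used as a baseline covariate.

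These are wording changes with no added visits or procedures, and are best made before any outcome data are examined by arm.

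Separately, reconcile the six time points with the five listed days, say whether the Day 180 draw is kept and where it is analysed, and clarify what the draws must precede. If a pre-treatment draw was intended, state it. A new Day 3 recording of HRV, BPV or C3 Logix is optional and not free: by the described procedure BPV takes 5 + 5 + 1 + 5 = 16 minutes, and HRV at least 5 + 1 + 5 = 11 minutes plus set-up. It would need an amendment and possibly an extra visit for usual care.
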